Models of diet-induced obesity in mice have shown that exercise improves, but does not reverse, damage imparted on oocytes as a result of a high fat diet [10]. A systematic review and meta-analysis of human studies found that exercise improved pregnancy rates (risk ratio 2.10, 95% CI: 1.32–3.35) in women with reproductive health problems like polycystic ovary syndrome (PCOS) [11]. Studies have also demonstrated promising maternal-fetal benefits of exercise during pregnancy such as improved physical fitness [12], more appropriate gestational weight gain [13], a decreased risk for preeclampsia and other pregnancy-specific diseases like gestational diabetes [14, 15], and decreased odds of macrosomia at birth without affecting the odds of growth-restricted, preterm, or low birth weight babies [12, 16, 17]. Studies have demonstrated that adherence to a Mediterranean diet, characterized by higher intake of unsaturated fats, lower intake of animal fats, and lower ratios of omega-6 to omega-3 fatty acids [18], is also associated with a reduced risk of many chronic diseases [19], improved fertility rates [odds ratio 1.4, 95% CI: 1.0–1.9] [20], as well as larger embryo yield in IVF [21], and better pregnancy outcomes [7, 20, 22, 23].

Despite the evidence of a healthier diet improving IVF procedure outcomes, there is little evidence on the molecular changes at the level of the oocyte or follicular fluid that occur due to alterations in diet, and virtually nothing is known about the impact of the combined effect of healthy diet and increased PA. Thus, we have designed a study with the primary objective of assessing the efficacy of a peri-conception nutrition and exercise intervention on mitigating obesity-associated changes in oocyte gene expression profiles and follicular fluid metabolites. Secondary objectives include determining the effect of the intervention on cumulus cells gene expression as well as the feasibility and acceptability of the intervention (using a standardized taxonomy [24]). To help address these objectives, overall metabolic health indices such as fitness, blood pressure, insulin sensitivity, triglycerides, C-reactive protein and interleukin-6 concentrations will be assessed.

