### Consent and randomization

The informed consent process will educate potential participants about the research study through IRB-approved methods. Eligible participants will be contacted, and a copy of the informed consent will be provided to the participant prior to signing consent documents. A research team member will reach out to potential participants 2 days prior to the scheduled visit to perform a COVID-19 screening and answer questions on the intervention components of the study. At the first visit, the research team will review all study procedures and the informed consent documents with the potential participant. Participants will be given sufficient time to review the consent form, ask questions, and receive clarification prior to signing any documents. If eligible and interested in enrollment, informed consent will be obtained from the participants and documented.

Women will be randomized, with computer generated randomization, to a standard of care group (*N* = 60) and an intervention group (*N* = 60). Due to the high incidence of obese women with Polycystic Ovarian Syndrome (15–30%) [26], compared with other infertility diagnoses, women will first be classified into one of two strata based on the presence or absence of PCOS. Within each stratum, the proposed study will randomize the enrolled participants into either the intervention group (*N* = 30) or the standard of care group (*N* = 30). Thus, the potential for confounders of infertility, besides PCOS, should be equally distributed between the groups and not affecting the main outcome of interests. The study will have four experimental arms: PCOS-standard of care, PCOS-intervention, no PCOS-standard of care, no PCOS-intervention. Allocation will happen at the second visit (after consent and the collection of baseline measures) by providing the participant with an opaque, sealed envelope containing their allocation.

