#### Statistical analyses

Prior to inferential analyses, exploratory data methods will be used to check for potential outliers and aberrant observations and measurements. The following will be tested between the PCOS and no PCOS groups to assess potential differences: fertility diagnosis (male factor, ovulatory disorder, tubal factor, endometriosis or unexplained), pregnancy, live birth, age and race using Mann-Whitney U nonparametric tests for each strata. Follicular fluid and serum metabolites will be analyzed using a one factor Analysis of Covariance (ANCOVA) at four levels because of the potential unbalanced data structure. Pair-wise comparisons using Tukey-Kramer post-hoc tests will be used to identify groups whose means differ significantly while retaining the family-wise error rate at 5%. If the distributional assumptions for ANOVA are not met, and if a suitable data transformation is not found, a Kruskal-Wallis equality-of-populations rank test will be used, followed by Dunn’s test of multiple comparisons. When the design is balanced, two-way ANOVA or non-parametric Friedman test will be used in data analysis. As alternatives, generalized linear models may be also used to test the effects of treatment and presence of PCOS and ANCOVA may also be used to control for additional confounding factors Correlations will be determined using the Pearson Product Moment or the Spearman Rank Order for non-parametric tests. Significance will be set at *p* < 0.05. RNA-seq data will be analyzed using SeqMonk and R software. Gene expression levels will be expressed as raw read counts for differential expression analysis and as log-transformed normalized reads per kilobase per million mapped reads for visualization. Differentially expressed gene expression will be identified using the DESeq2 package and filtered at ± two-fold change and statistical significance with a *p* value ≤0.05. Gene Ontology (GO), transcription factor (TF) target analysis, and pathway analyses will be conducted with DAVID bioinformatics and/or WebGestalt, which include multiple testing corrections. For participants assigned to the standard of care whose fertility treatments were unsuccessful, they will be offered to re-enroll and be directly assigned to the intervention group. The data from these participants will be analyzed separately, using paired t-tests or non-parametric equivalent to evaluate the effect of the intervention (pre and post).

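### For the metabolites, the overall intervention versus standard-of-care contrast is not the fixed test: the lead analysis is an all-pairs comparison of four treatment-by-PCOS cells

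*Protocol article*

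**What the plan says.** The Background section gives a "primary objective of assessing the efficacy of a peri-conception nutrition and exercise intervention" on oocyte gene expression and follicular fluid metabolites, without dividing it by PCOS status. The Discussion words the expected results the same way, as intervention against standard of care.

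Under Consent and randomization, "women will first be classified into one of two strata based on the presence or absence of PCOS", and within each stratum they are randomised to intervention or standard of care, 60 against 60 overall. The same section adds: "The study will have four experimental arms: PCOS-standard of care, PCOS-intervention, no PCOS-standard of care, no PCOS-intervention".

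Under Statistical analyses, metabolites in follicular fluid and serum "will be analyzed using a one factor Analysis of Covariance (ANCOVA) at four levels because of the potential unbalanced data structure". Tukey-Kramer tests then serve to "identify groups whose means differ significantly while retaining the family-wise error rate at 5" per cent. The abstract repeats this analysis. Two further sentences bear on the overall effect:

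- One is conditional: "When the design is balanced, two-way ANOVA or non-parametric Friedman test will be used in data analysis".
- The other offers an option: "generalized linear models may be also used to test the effects of treatment and presence of PCOS".

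**The concern.** Randomisation within PCOS strata supports one main question: does the intervention change the metabolite? The lead analysis puts a different one: which of four cells differ from each other? The six pairs divide as follows:

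- Two compare intervention with standard of care within a stratum. These are randomised.
- Four compare a PCOS cell with a no-PCOS cell. These are not randomised, yet they share the 5% family-wise error.
- None is intervention against standard of care overall.

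The overall contrast depends on how many evaluable women each cell turns out to have, or on a choice left open. Two things are at stake. A real effect of moderate size could be missed because each within-stratum test uses half the women at a stricter threshold. And the test on which the metabolite conclusion rests can be picked after the data are seen.

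**Working it through.** **Inputs.** From Sample size: 20 evaluable women per cell, 30 enrolled per cell, power 0.80, significance level 0.05. The article does not state sidedness; two-sided is assumed. The SD is set to 1, and the effect is assumed to be the same in both strata.

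**The plan's own figure.** Sample size states a detectable mean difference of 0.37 SD with 20 per group. This does not reproduce: 20 against 20 detects 0.91 SD (two-sided t test), and power at 0.37 SD is 0.21. That is a separate matter. The figures below use the planned cell size, not the 0.37.

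**Detectable difference at 20 per cell (80 − 4 = 76 df).** Approximately, d = (critical t + t for 80% power) × √(2/n), with n the women on each side and 0.846 the 80% point of t on 76 df.

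- Tukey pair, 20 v 20: the critical value is q(0.05; 4, 76)/√2 = 2.627. So d ≈ (2.627 + 0.846) × √(2/20) = 3.473 × 0.3162 = 1.10 SD. The per-pair significance level is about 0.0104.
- Treatment main effect, 40 v 40: the critical value is 1.992. So d ≈ (1.992 + 0.846) × √(2/40) = 2.838 × 0.2236 = 0.63 SD.

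The exact noncentral t results are 1.100 and 0.6345, a ratio of 1.73. To give one Tukey pair 80% power at 0.63 SD would need about 59 per cell (236 evaluable women) instead of 20 (80).

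**Power at a common effect of 0.63 SD**

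| Test | 20 per cell | 30 per cell |
|---|---|---|
| Treatment main effect | 0.80 | 0.93 |
| Four-level omnibus F | 0.63 | 0.83 |
| Tukey, one given stratum | 0.27 | 0.44 |
| Tukey, at least one stratum | 0.47 | 0.69 |
| Tukey, both strata | 0.08 | 0.20 |

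The either-stratum figure is simulated. As a check, treating the two strata as independent gives 1 − (1 − 0.274)² = 0.47. At 30 per cell the detectable differences are 0.89 SD (Tukey pair) and 0.52 SD (main effect).

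**Does imbalance prevent a treatment + PCOS model?** With n1 and n0 women per arm in a stratum, the variance of the adjusted treatment estimate is σ² / Σ[n1·n0/(n1 + n0)], summed over the strata. With 20 in every cell the sum is 10 + 10 = 20. Suppose instead that 30% of 80 evaluable women had PCOS, the upper end of the 15–30% that the article cites. The cells would be 12, 12, 28 and 28, and the sum 6 + 14 = 20. The main effect keeps its power of 0.80, while the Tukey pairs fall to 0.15 (PCOS) and rise only to 0.40 (no PCOS). Unequal strata are a reason to use the model, not to avoid it.

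**How likely is balance?** The article gives no loss rate for fluid or serum. Assuming independent loss from 30 women per cell, the chance that all four cells end equal is the sum over counts of (binomial probability)⁴. That is about 2.0% at 5% loss, 0.7% at 10%, and 0.2% at the 33% that the article expects for oocytes.

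**The case against.** The strongest reply is that the overall effect is not absent. The section commits to a two-way ANOVA when the design is balanced and names a generalized linear model for treatment and PCOS. A reader might infer that the overall contrast is never tested; the text does not support that. What stands is that one route depends on balance and the other is optional. The planned enrolment is equal, so the balance condition could be read as already met. But the four-level model is adopted because the data may be unbalanced, which points to the cells as they turn out.

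Second, a four-level factor is the same model as treatment by PCOS with interaction, so the overall contrast can be estimated from it. True, but the plan names the pairwise tests, not that contrast.

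Third, four arms and per-cell sizing are stated design features. If the effect occurred in one stratum only, the main effect would be half of it: the effect in that stratum would have to reach about 2 × 0.63 = 1.27 SD to be detected at 20 per cell, against 1.10 SD for the Tukey pair. So the ranking depends on a broadly common effect, which is how the objective and the Discussion are framed.

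Fourth, a reader might infer that most of the power is lost. That fits a single given stratum (0.27 against 0.80), but not at least one stratum (0.47) or the omnibus F (0.63). The omnibus F, however, also reacts to PCOS differences, so a significant result would not show that the intervention worked.

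Fifth, the 33% loss concerns good-quality oocytes. Follicular fluid may be obtained when no oocyte is spare, and serum does not depend on oocyte yield. The 30-per-cell figures may therefore be nearer the truth, although Sample size itself applies 20 per group to follicular C-reactive protein and insulin.

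Finally, gene expression, the other primary outcome, is analysed with DESeq2 and is untouched by this point. The absence of a named covariate list is what an article may leave to the full plan, and is no finding.

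**Conclusion.** The point holds for the follicular fluid and serum metabolites. The plan does not fix the overall randomised contrast as the test, leads with a family in which four of six comparisons are not randomised, and gives imbalance as a reason when it is not a valid one.

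The cost is a detectable difference of 1.10 SD for a within-stratum Tukey pair against 0.63 SD for the main effect at 20 per cell, or 0.89 against 0.52 SD at 30. These figures assume a common effect and SD in both strata, a two-sided 5% level and no gain from covariates. The objection to the choice of contrast and to its stated reason does not depend on them.

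**What to change.** In Statistical analyses, state that the primary test for each metabolite is the treatment coefficient, with 95% CI and a two-sided 5% level, from a linear model with treatment and PCOS stratum, used whether or not the cells are balanced. Add the baseline value of the same analyte where it is measured, as for serum analytes drawn at Visits 1 and 3. Follicular fluid is collected only at retrieval and has no baseline of its own, and the article gives no serum-to-fluid correlation that would support using serum as a substitute throughout.

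Report the treatment-by-PCOS interaction and the within-stratum contrasts as secondary. Drop the all-pairs Tukey-Kramer procedure as the lead test, and remove the rule that switches models according to balance. Change the abstract to match.

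The cost is a change of wording before the data are analysed. No new sample, visit or participant is needed, and the stratum-specific results are kept. The price is that an effect confined to one stratum would no longer be the target of the lead test.

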**Methods:**

This single blinded randomized control trial will include 120 women with a BMI of 25–45 kg/m^2^, ≥21 years of age, and undergoing in vitro fertilization (IVF) treatments. Participants will be randomized to standard of care (*N* = 60) or an intervention group (*N* = 60) in a block design by polycystic ovary syndrome status. The intervention will combine a dietary component (Mediterranean meal plan) with exercise prescription following the Physical Activity Guidelines for Americans. Participants will be assessed pre- and post-intervention. The standard of care group will be offered to join the intervention group if the IVF treatments are unsuccessful as a cross over design. Recruitment is anticipated to start in July of 2021. Primary outcomes will include single oocyte gene expression profiles and follicular fluid metabolites. Mann-Whitney U nonparametric tests will be used to assess potential differences for each stratum. Follicular fluid and serum metabolites will be analyzed using a one-factor Analysis of Covariance (ANCOVA) at four levels, pair-wise comparisons using Tukey-Kramer post-hoc tests will be used to identify groups whose means differ significantly while retaining the family-wise error rate at 5%. When the design is balanced, two-way Analysis of Variance (ANOVA), or non-parametric Friedman test will be used in data analysis. Additionally, general linear models and ANCOVA may be used to control for covariates. Significance will be set at *p* < 0.05. Findings will be disseminated via peer-reviewed manuscripts and presentations at scientific conferences.

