##### Biological samples

Blood samples, up to 35 ml, will be collected from the participants at visits 1 and 3 by a trained phlebotomist under overnight fasted conditions. During the entire study, we will collect up to 70 ml total. Blood samples will be centrifuged to separate plasma, serum, and red blood cells. Blood samples will be used to assess glucose, insulin, HOMA-insulin resistance score, interleukin-6, C-Reactive Protein, tumor necrosis factor, leptin, lipid profiles or any other biomarkers or analytes of interest using ELISA, electrochemiluminescence (ECL), colorimetric assays, metabolomics or any other appropriate methodology. Urine and stool collection will be obtained to evaluate metabolites, hormones or bacteria/microbes. Samples will be obtained using sterile collection cups. All biological samples will be aliquoted and stored at − 80 °C until further analyses.

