##### Oocyte, cumulus cell, and follicular fluid data collection

AF&GA will provide the research team with oocytes (eggs), cumulus cells (cells surrounding the egg), and follicular fluid (liquid surrounding the egg that also contains granulosa cells) that are not needed for the IVF procedures (e.g., too many eggs retrieved). These samples will be collected during the standard oocyte retrieval procedures performed as part of standard care for the participants undergoing fertility treatment. Participants will undergo standard procedures at AF&GA for ovarian stimulation, which include hormonal superovulation and oocyte retrieval 36 h after human gonadotropin injection. Any deviations from the standard clinic procedures will be documented and sensitivity analyses will be performed to determine whether deviations to stimulation protocol yielded in significant differences. It is possible that the research team will not obtain samples in the case that the retrieval yields only enough eggs for the IVF procedures. In this case, only follicular fluid will be obtained. The research team will not obtain samples that could have been fertilized or frozen as agreed with the participant prior to the retrieval procedure. The research team will obtain only samples that are unneeded by the clinic. Thus, no additional treatment or clinical procedures will be required for the participants. The embryologist at the clinic will collect the cumulus cells during the processing of the oocytes. Granulosa cells will be isolated from the follicular fluid by centrifugation at 4000 rpm for 10 min. Follicular fluid samples contaminated with blood will not be used for analysis. Samples will be placed on ice and transported by the research team to the ACNC where they will be stored in messenger RNA lysis buffer and frozen at − 70 °C until processing. Oocytes and cumulus cells will be used to study gene expression while follicular fluid will be used to measure metabolites and hormones that may be influenced by diet and exercise. Both mRNA and genomic DNA will be isolated from individual oocytes as previously described [9]. cDNA libraries will be prepared and fragmented cDNA will be evaluated to determine size distribution of the libraries. Samples will be sequenced using the NextSeq 500 System (Illumina). Individual libraries will be generated and RNA-Seq will be conducted. Sequencing reads from each sample will be trimmed and filtered before being aligned to the human genome (hg19). All data will be analyzed using SeqMonk and R software. Differentially expressed gene expression will be identified using the DESeq2 package which will include multiple testing corrections. Serum and follicular fluid glucose, total cholesterol, and triglyceride levels will be assessed using colorimetric or electrochemiluminescence assays. Serum and follicular fluid insulin, leptin, tumor necrosis factor (TNF)-α, C-reactive protein (CRP), and interleukin-6 will be measured using enzyme-linked immunosorbent or electrochemiluminescence assay kits. Serum lipid profiles—non-esterified fatty acids, high-density lipoprotein, and low-density lipoprotein— will be analyzed by enzymatic methods on a clinical analyzer. All assays will be performed in accordance with the manufacturers’ instructions.

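### The Friedman test, named as the rank option beside two-way ANOVA, does not in its ordinary form fit four groups of unmatched women

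*Protocol article*

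**What the plan says.** The Statistical analyses section of the protocol article gives two routes for the metabolite outcomes.

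- **Main route, chosen because the data may be unbalanced:** "Follicular fluid and serum metabolites will be analyzed using a one factor Analysis of Covariance (ANCOVA) at four levels", with Tukey-Kramer comparisons. If the distributional assumptions fail and no transformation helps, "a Kruskal-Wallis equality-of-populations rank test will be used, followed by Dunn’s test of multiple comparisons".
- **Balanced route:** "When the design is balanced, two-way ANOVA or non-parametric Friedman test will be used in data analysis". The Abstract (Methods) has the same wording: "or non-parametric Friedman test will be used in data analysis". Neither place says what the block is, whether a cell holds one observation or many, or which effect is tested.

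On the design, Consent and randomization says that "women will first be classified into one of two strata based on the presence or absence of PCOS", with individual randomization inside each stratum, and that "The study will have four experimental arms: PCOS-standard of care, PCOS-intervention, no PCOS-standard of care, no PCOS-intervention". On follicular fluid, oocytes and cumulus cells, the data collection section says: "These samples will be collected during the standard oocyte retrieval procedures performed as part of standard care". Table 1 lists that collection at retrieval only. Serum is drawn twice: "Blood samples, up to 35 ml, will be collected from the participants at visits 1 and 3". Standard-of-care women who later re-enroll are analyzed separately with paired tests.

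**The concern.** The Friedman test is the rank analogue of a two-way layout in which each row is a block of related observations, such as one woman measured under several conditions or a matched set. It ranks within rows and sums over them. It is not the general rank counterpart of a two-way ANOVA with two between-subject factors.

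Here the four cells hold different women, and nothing links a woman in one cell to a woman in another. An analyst following the sentence literally must either reduce each cell to one number or build rows from unrelated women. The first cannot reach significance. The second yields a p-value that changes when the data file is sorted differently. Follicular fluid metabolites are a primary outcome, and Friedman is the only rank test named for the balanced layout of 30 per cell that the design plans. So the matter deserves correction even though it concerns one optional route.

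**Working it through.** **Inputs from the article.** Four groups, as 2 PCOS strata by 2 treatments; 30 enrolled per group; about 33% expected to yield no good-quality oocyte; at least 20 per group intended; alpha 0.05 (taken as two-sided, since sidedness is not stated). The planned group size reproduces: 20/(1 − 0.33) = 29.9, rounded up to 30. The checks use 20 per cell.

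**Assumptions, not in the article.** Normal data for the power runs; a treatment effect of 0.63 SD, which is what 40 against 40 detects with 80% power: (1.960 + 0.842) × √(2/40) = 0.63; a PCOS shift of 1 SD where one is mentioned.

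**Reading 1: PCOS as block, one summary per cell.** With b = 2 blocks and k = 2 treatments, the statistic is 12/[bk(k+1)] × ΣR² − 3b(k+1). The most extreme rank sums are 2 and 4, giving 12/12 × (4 + 16) − 18 = 2. The chi-square tail on 1 degree of freedom at 2 is 0.157, and the exact p is 2 × (1/2)² = 0.5. No data can give p < 0.05.

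**Reading 2: unrelated women paired within stratum (40 pairs, two columns).** With k = 2, Friedman is a sign test: (n₊ − n₋)²/40.

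- A split of 27 to 13 gives 14²/40 = 4.9 (p = 0.027); 26 to 14 gives 12²/40 = 3.6 (p = 0.058). Rejection therefore needs 27 or more of 40 in one direction.
- Exact type I error: 2 × P(Bin(40, 0.5) ≥ 27) = 0.038. Simulation gave 0.040.
- At 0.63 SD, a treated woman exceeds an unrelated control with probability Φ(0.63/√2) = 0.672. Power is then P(Bin(40, 0.672) ≥ 27) = 0.56. Simulations gave 0.55 to 0.57.

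**Reading 3: unrelated women in rows of four (20 rows, four columns).** Type I error is 0.048. Power at 0.63 SD is 0.49, against 0.59 for Kruskal-Wallis on the same groups. This form does not isolate treatment: a 1 SD PCOS difference with no treatment effect at all rejects in 90% of runs.

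**Row order.** For the four-column form at 0.63 SD, 200 simulated data sets were each reshuffled 300 times within groups. In 90% of them the result moved between p < 0.05 and p ≥ 0.05, with a median p range of 0.001 to 0.45. Separate runs of the same kind gave 92% and, for pairs within stratum, 95%. At 0.9 SD the four-column figure was 68%.

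**Reading 4: PCOS as block, women as replicates.** Rank the 40 women in each stratum together and sum the ranks of one treatment over both strata. The null mean is 2 × 20 × 41/2 = 820 and the variance is 2 × 20 × 20 × 41/12 = 2733. Type I error is 0.051 and power at 0.63 SD is 0.77. In a worked data set, p was 0.0044 in every one of 300 reshufflings. The van Elteren weights depend only on stratum size, so with equal strata they cancel and the two statistics coincide. Three simulated data sets gave 6.668, 7.481 and 2.226 by both formulas.

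| Form, 20 per cell | Type I error | Power at 0.63 SD | Depends on row order |
|---|---|---|---|
| Friedman, arbitrary pairs | 0.040 | 0.55 | yes |
| Friedman, arbitrary rows of four | 0.048 | 0.49 | yes |
| Replicated Friedman / van Elteren | 0.051 | 0.77 | no |

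**The case against.** The best defense is that a balanced layout with PCOS as block and women as replicates has a legitimate Friedman-type test (Mack-Skillings), and that the balance condition hints at it. If that is meant, the analysis is sound and order-free. This stands as far as it goes, but the text names neither block nor replication, and the test as ordinarily known and programmed takes one observation per cell. A condensed article may leave such detail to a fuller document. The difficulty here is not an omission, though: the test it does name does not fit in its usual form.

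A second defense is that the route is remote. It needs balanced cells and then a preference for Friedman over two-way ANOVA. The article itself foresees imbalance, and losses at retrieval make exact balance unlikely. That also stands, and it limits the consequence. The main four-group analysis already has a suitable rank fallback in Kruskal-Wallis with Dunn's test, so a reader should not infer that the primary outcome has no usable rank analysis.

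A reader might also infer that the test inflates false positives, or that its result depends on sorting under every reading. Neither is supported: type I error stays at or below about 5% with arbitrary rows, and the replicated form has no order dependence.

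Finally, the two serum draws do not supply the missing blocks. Friedman on two visits within a woman tests change over time, not treatment, and the sentence is not tied to those visits.

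**Conclusion.** The concern holds in a limited form. The ordinary Friedman test is the wrong rank counterpart for a two-way layout of independent women. Its faults here are arbitrariness, a loss of about 20 percentage points of power against a stratified rank test and, with four columns, a test that mixes the PCOS effect with treatment. Collapsed to cell summaries, it cannot reject.

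The 0.157 bound is exact arithmetic on the chi-square approximation. The power and re-ordering figures rest on the assumed 0.63 SD effect and 20 women per cell, and would change with either. The practical effect is confined to the case where the cells are balanced and this option is chosen. The wording should be corrected before analysis; the randomized design itself is unaffected.

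**What to change.** In the Abstract (Methods) and in Statistical analyses, replace the Friedman test with the van Elteren test (Wilcoxon rank-sum stratified by PCOS status) of intervention against standard of care. It works with equal or unequal cells, so the balance condition need not apply to this rank test. The condition on two-way ANOVA can stay. Keep Kruskal-Wallis with Dunn's test as the fallback for the four-group analysis.

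If the replicated Friedman test was intended, saying so, with PCOS as block and women as replicates, would also resolve the point, but only for equal cells.

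There is one drawback. The van Elteren test addresses the treatment effect only, not the PCOS effect or the treatment-by-PCOS interaction. Its replicated-Friedman equivalent picked up a crossing interaction of +0.9 and −0.9 SD in only 2% of runs. If those effects are wanted on ranks, name a rank-based two-way model, such as an aligned-rank analysis, as well.

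The cost is two sentences and standard software, with no additional participants or data.

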#### Sample size

Based upon existing data in the literature, a power of 0.8, and a *p*-value set at 0.05, with 20 women per group, we will be able to detect a mean difference of at least 0.37 standard deviation units in follicular levels of C-reactive protein and of insulin. In our previous study, we found follicular fluid CRP differences of 3.2 μg/ml (2.7 vs. 5.9 μg/ml, respectively) between normal weight and obese women [12]. Thus, we are confident that this sample size will be sufficient to detect clinically meaningful differences. Based on our experience, we expect that we will be unsuccessful in obtaining a good quality oocyte from approximately 33% of women enrolled. Therefore, we will enroll 30 women in each of the 4 groups (PCOS- standard of care, PCOS-intervention, no PCOS- standard of care, no PCOS-intervention) to assure that we will have at least 20 oocytes per group.

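### Correlations are planned as plain Pearson or Spearman tests with no term for arm or PCOS; if the four groups are pooled, shared group shifts can appear as association (minor)

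*Protocol article*

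**What the plan says.** The protocol article gives correlations one sentence, under Statistical analyses: "Correlations will be determined using the Pearson Product Moment or the Spearman Rank Order for non-parametric tests". The next sentence is general: "Significance will be set at *p* < 0.05". The article does not name the variables to be correlated or the visit, and it does not say whether the women are taken together or group by group.

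The group structure is fixed elsewhere. Under Consent and randomization, "women will first be classified into one of two strata based on the presence or absence of PCOS", and then "The study will have four experimental arms: PCOS-standard of care, PCOS-intervention, no PCOS-standard of care, no PCOS-intervention". Under Sample size, "Therefore, we will enroll 30 women in each of the 4 groups". That makes 120 women, 60 with PCOS and 60 without.

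The comparisons of group means in the same section do use this structure: a four-level ANCOVA, a two-way ANOVA when balanced, and optional generalized linear models for treatment and PCOS. The correlation sentence is not tied to any of these.

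**The concern.** Pearson and Spearman coefficients computed on all women mix two things: association among women of the same group, and differences between the group means. In this trial the second part may be appreciable. Women with PCOS make up half the sample by design, against the 15–30% frequency that the article quotes. The Discussion also expects the intervention to move fitness, insulin sensitivity, triglycerides, blood pressure, systemic inflammation and a follicular fluid metabolite in the same women.

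Two variables that both move with PCOS, or both with treatment, will then tend to correlate in the pooled sample even if neither tells anything about the other within a group. Shifts in opposite directions give a spurious negative correlation, or hide a real positive one. A significant pooled coefficient could be read as a link between, say, a serum marker and a follicular fluid marker when it only restates the group difference.

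**Working it through.** **The plan's own figures.** The article gives no figure for the correlations, so there is none to reproduce. The group size does reproduce: 20 evaluable women per group and 33% loss give 20/(1 − 0.33) = 29.9, rounded up to 30. The two sample sizes below follow from it: 4 × 20 = 80 evaluable and 4 × 30 = 120 enrolled. The 0.37 SD in the Sample size section serves below only as one small reference shift. Whether it is right as a detectable difference is a separate matter.

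**Inputs.** Four equal groups and a 0.05 level come from the article. A two-sided test is assumed. The shifts dP (PCOS) and dT (treatment), in within-group SD units and equal for both variables, are assumptions. The within-group correlation is set to zero.

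**Pooled correlation.** With each factor splitting the sample in half, the between-group variance, and likewise the covariance, is v = (dP² + dT²)/4. The pooled correlation is therefore ρ = v/(1 + v).

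- 0.37 SD, PCOS only: v = 0.1369/4 = 0.034; ρ = 0.034/1.034 = 0.03
- 0.5 SD, both factors: v = 0.50/4 = 0.125; ρ = 0.125/1.125 = 0.11
- 0.8 SD, PCOS only: v = 0.64/4 = 0.16; ρ = 0.16/1.16 = 0.14
- 1 SD, PCOS only: v = 1/4 = 0.25; ρ = 0.25/1.25 = 0.20

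The half-and-half mix adds to the effect. For PCOS prevalence p, v = p(1 − p)dP². At 0.8 SD, p = 0.15 gives 0.0816/1.0816 = 0.08 and p = 0.30 gives 0.1344/1.1344 = 0.12, against 0.14 at p = 0.50.

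**Rejection rates.** Simulation, 10,000 to 20,000 trials per setting, two-sided Pearson test at 0.05:

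| Assumed shift in both variables | Pooled, n = 80 | Pooled, n = 120 | Adjusted for four groups |
|---|---|---|---|
| none | 5.0% | 5.0% | 5% |
| 0.25 SD, PCOS only | 4.9% | 5.1% | 5% |
| 0.37 SD, PCOS only | about 6% | about 6.5% | 5% |
| 0.5 SD, PCOS only | 8% | 10% | 5% |
| 0.37 SD, both factors | 8.5% | 10.6% | 5% |
| 0.5 SD, both factors | 16–17% | 23% | 5% |
| 0.8 SD, PCOS only | 23% | 33% | 5% |
| 1 SD, PCOS only | 43–44% | 60–61% | 5% |

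The adjusted column is the correlation of residuals from the four group means on n − 5 degrees of freedom. It lay between 4.5% and 5.3% throughout. Spearman was within about 3 points of Pearson, so moving to ranks does not help.

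**Hand check of the last row (Fisher z).** The critical |r| is 0.220 at n = 80 and 0.179 at n = 120. With ρ = 0.20 (z = 0.203), the distance at n = 80 is (0.203 − 0.224) × √77 = −0.18, giving 43%. At n = 120 it is (0.203 − 0.181) × √117 = 0.23, giving 59%. Both agree with the simulation to within two points.

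**The case against.** The strongest objection is that the article does not say that the women are pooled. Correlations computed within each group fit the sentence equally well and would be free of the problem. This stands as a limit on the claim. Pooling is the natural reading of an unqualified sentence, but it is a reading.

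Second, an article commonly leaves the variables and the analysis set of ancillary correlations to the full protocol or analysis plan, which is not shown. That is accepted, and no missing detail is held against the article. The point concerns the method that it does name, for which a better one is available from factors the trial already stratifies and randomises by.

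Third, a marginal correlation in a mixed sample is a real association. Calling its detection a type I error assumes that the within-group correlation is the target. Removing arm effects also removes covariation that the intervention produced, which the investigators may want to describe. This stands too, and is why the unadjusted coefficient need not be banned, only labelled.

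Fourth, the size rests on assumed shifts, and at 0.37 SD or less on a single factor there is almost no inflation. A reader might infer from the 1 SD row that false associations are bound to appear and that many reported correlations would be significant for this reason alone. The documents do not support that: they give no PCOS or treatment shift for any pair of variables.

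A reader might also infer that the trial's conclusions depend on these correlations. They do not. The stated objectives concern the effect of the intervention on oocyte and cumulus cell expression and follicular fluid metabolites, and feasibility and acceptability.

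**Conclusion.** The concern holds in a conditional form. The stated method has no term for arm or PCOS in a sample constructed from four groups. If the women are pooled, group shifts common to two variables can produce a significant correlation with no association within any group. The consequence ranges from negligible (about 6% rejections for 0.37 SD on PCOS only) through moderate (16–17% at n = 80 and 23% at n = 120 for 0.5 SD on both factors) to large (43–44% and 60–61% for 1 SD on PCOS only).

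These figures assume equal groups, additive shifts of the same size and direction in both variables, normal data and zero within-group correlation. The n = 120 figures also assume that every enrolled woman contributes both measurements. The correlations are ancillary, so this is a minor improvement and does not threaten the primary analysis.

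**What to change.** Replace the correlation sentence with one that specifies partial Pearson correlations, or rank-based partial Spearman correlations where distributions require it, adjusted for randomised arm and PCOS. In practice, take residuals from the four group means (of the values or of their ranks), correlate them, and test on n − 5 instead of n − 2 degrees of freedom. If an unadjusted pooled coefficient is also shown, label it as descriptive and say that it mixes between-group and within-group association.

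The cost is one sentence and three degrees of freedom. The critical |r| rises from 0.220 to 0.224 at n = 80 and from 0.179 to 0.182 at n = 120. No new data are needed, and the change should be made before the analysis begins.
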